### Study goals and objectives

The aim of this randomised feasibility trial will be to assess feasibility of a future definitive RCT on the effectiveness of the MiLES intervention in terms of recruitment, reach, and acceptability of the study protocol. Secondary, the study will also aim to evaluate the effectiveness of the online toolbox targeting employers on successful RTW of employees with cancer and to determine the sample size needed in a future definitive RCT on the effectiveness of the MiLES intervention. The online toolbox will be considered effective if the intervention group improved significantly more on both components of the primary outcome measure ‘successful RTW’: the number of participant in the intervention group that have returned to work is higher compared with the control group, provided that their degrees of successfulness of RTW is also significantly higher.

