### Methodology

Interventions: the intervention consists of an online toolbox targeting the participant’s employer. With ‘employer’ we refer to the person who is, from his/her role as (direct) supervisor, human resource manager or case-manager, in direct contact with the participant and from there responsible for guiding the participant at work. The online toolbox is an open-assess website containing to-the-point information, videos and checklists to support employers during the RTW process of an employee diagnosed with cancer.

Intervention group: participants randomised in the intervention group will be asked to inform their employer about the online toolbox, either by email or letter. Employers will be asked to use the online toolbox throughout the RTW process of the participant.

Control group: participants randomised to the control group will not inform their employer about the online toolbox for a period of six months.

Primary outcome measure: feasibility of a future definitive RCT on the effectiveness of the MiLES intervention (in terms of reach, appropriateness of inclusion criteria, recruitment rate and appropriateness of the study protocol).

Primary effect measure: the primary effect measure of the intervention is the combined effect measure successful RTW. This effect measure is a combination of RTW (having performed work activities in own work or in replacement work during the past four weeks) and a subgroup analyses for the ones that did return to work: degrees of successfulness of RTW (a new weighted, on individual level, outcome measure) (7). The degree of successfulness of RTW contains seven items, which were found to constitute successful RTW most importantly, according to employees diagnosed with cancer: ‘enjoyment in work’, ‘work without sacrificing health’, ‘open communication with employer’, ‘perceived confidence from employer without assumptions about workability’, ‘feeling welcome at work’, ‘good work-life balance’ and ‘joint satisfaction about the work situation (employer and employee)’. Each participant rates each items on its perceived importance and on its success. The combination of the items’ relative perceived importance and the items’ success determines the degrees of successfulness of RTW.

Secondary effect measures: Quality of Working life (QWLQ_CS) (8) and number of unwanted work changes (#).

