Time points data collection: baseline, before randomisation [T0], after 3 months of follow up [T1] and after six months of follow up [T2].

Randomization: using the electronic data-capture system Castor; allocation ratio will be set at 2:1 (intervention vs. control group); controlled the participant’s RTW status; neither the participant nor the research team will be blinded for the randomization.

Graphic outline: see figure 1.

[figure not shown]

**Figure 1.** Graphic outline of the study design and procedures using a flow diagram.

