### Data management and statistical analysis

Feasibility: a future definitive RCT to study the effectiveness of the MiLES intervention will be considered feasible when all of following criteria are met:

1. Criterion for appropriateness of inclusion criteria and for recruitment: ≥ 70% of the individuals who gave permission for telephone contact are willing to participate in the study;
2. Criterion for appropriateness of protocol: ≤ 20% do not want to participate due to the randomization procedure or are lost to follow-up due to randomization in the control group;
3. Criterion for appropriateness protocol: ≤ 20% of the participants are not willing to inform their employer about the online toolbox after randomization into the intervention group;
4. Criterion for retention rate: ≤ 20% of the participants are lost to follow-up; and,
5. Criterion for reach: the sample size number of 90 participants is included within the recruitment period of six months, starting when the first individual is invited by their treating physician.

Effect measures: equal distribution between the intervention and control group at baseline will be determined using chi-square tests for categorical variables and Student’s t-tests (normally distributed variables) or Mann-Whitney U tests (not normally distributed variables) for continuous variables. When no statistically significant unequal distributions will be found at baseline, the relative risk (RR) will be determined for RTW at T1 and T2, and a longitudinal multilevel analysis will be performed with the group classification as an independent variable and I-RTW_CS scores at the different time point (T0, T1 and T2) as dependent variables.

In the event of significant imbalance of a prognostic factor for the primary effect measure at baseline (9, 10), this factor will be used as a covariate for the analysis of that effect measure. In that case, a logistic regression analysis will be used to examine differences between the intervention and the control group with regard to RTW. For the subgroup of participants who did return to work, a longitudinal multilevel analysis will be performed to examine the difference between both groups with regard to I-RTW_CS scores. We hypothesised that participants in the intervention group 1) returned to work more often and 2) with a higher I-RTW_CS score, compared to the control group.

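### The degree of return-to-work success is compared only among those who returned after randomisation, so it is open to selection bias of unknown direction, yet the effectiveness rule depends on it

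*Protocol*

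**What the plan says.** The protocol's Methodology section builds the primary effect measure from two parts. The first is RTW, defined as "having performed work activities in own work or in replacement work during the past four weeks". The second is "a subgroup analyses for the ones that did return to work: degrees of successfulness of RTW", scored by I-RTW_CS.

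The section on data management and statistical analysis gives two routes:

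- Without baseline imbalance, a longitudinal multilevel model takes "I-RTW_CS scores at the different time point (T0, T1 and T2) as dependent variables". The restriction to returners is not repeated here.
- With imbalance of a prognostic factor, the restriction is explicit: "For the subgroup of participants who did return to work, a longitudinal multilevel analysis will be performed to examine the difference between both groups".

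The definition in Methodology covers both routes, so it is the firmer source for the restriction.

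The same analysis section hypothesises that "participants in the intervention group 1) returned to work more often and 2) with a higher I-RTW_CS score". Study goals and objectives, and the Project summary in the same terms, call the toolbox effective if "the intervention group improved significantly more on both components of the primary outcome measure". More participants must return, "provided that their degrees of successfulness of RTW is also significantly higher".

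**The concern.** Membership of the analysed group is settled after randomisation, by an event that the intervention is meant to change. If the first hypothesis is true, the intervention arm's returners include people who would not have returned under control, and the control arm has no counterpart to them. A difference in mean I-RTW_CS then mixes any effect on success with a difference in who is being scored. Controlling the randomisation for RTW status balances status at T0; it cannot balance later return.

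The protocol gives no score for non-returners and no analysis of success over all randomised participants, and it does not caution about selection. It nevertheless makes this comparison one of two conditions for calling the toolbox effective. Preliminary effectiveness and the sample size for the definitive trial are both stated aims, so a selected-subgroup estimate could pass into that trial's design.

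**Working it through.** **No figure to reproduce.** The protocol gives a target of 90 participants without a significance level, power, SD, RTW rate or effect size. The calculations below show only how large the problem could be.

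**Inputs from the protocol.** 90 participants; "allocation ratio will be set at 2:1 (intervention vs. control group"), which gives 60 and 30; loss to follow-up of at most 20%. At 20% loss, 60 × 0.8 = 48 and 30 × 0.8 = 24 are followed.

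**Assumptions.** RTW of 70% versus 50%. Each participant has a normally distributed propensity to return and returns if it exceeds an arm-specific cut-off. The score has SD 1 and correlation ρ with that propensity. There is one time point, and a component succeeds if it is significant at two-sided 5% in favour of the intervention.

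**Step 1: shift in the returner comparison with no true effect on success.** With φ the normal density and c the cut-off for return rate p, the mean score of returners is ρ × φ(c)/p.

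- p = 0.70: c = -0.5244, φ(c)/p = 0.3477/0.70 = 0.4967
- p = 0.50: c = 0, φ(c)/p = 0.3989/0.50 = 0.7979
- Shift = ρ × (0.4967 - 0.7979) = -0.301 × ρ

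| ρ | -0.3 | 0 | 0.3 | 0.5 | 0.7 |
|---|---|---|---|---|---|
| Shift (SD) | +0.09 | 0 | -0.09 | -0.15 | -0.21 |

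The shift is zero if ρ = 0 or if RTW is equal in both arms.

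**Step 2: power of the returner comparison with a true effect of +0.5 SD.** Expected returners are 48 × 0.70 = 33.6 and 24 × 0.50 = 12. At ρ = 0 the standard error is √(1/33.6 + 1/12) = 0.336. The ratio is 0.5/0.336 = 1.49, and normal-approximation power is about 32%. Simulation with t-tests gives:

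| ρ | -0.3 | 0 | 0.5 |
|---|---|---|---|
| Power, score in returners | 42% | 30% | 19% |

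**Step 3: the joint rule.** Simulated power for RTW alone is about 38%. At ρ = 0 the two tests are close to independent, so both succeed in roughly 0.38 × 0.30 = 11% of trials; simulation gives 10 to 11%. At ρ = 0.5 it is about 6%. Thus the rule has little power even with no selection bias. Selection at ρ = 0.5 takes it from about 10% to 6%.

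**The case against.** Four points can be made for the plan.

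1. *Bias is not shown, and its direction is not known.* A reader might infer that the comparison is biased against the toolbox, because harder cases are helped back and lower the average. That needs a difference in RTW between arms and a positive link between propensity to return and score. The protocol gives neither figure, and at a negative correlation the shift favours the intervention. This stands: the supportable statement is that the comparison is open to selection bias.

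2. *Part of the group is protected.* Partially sick-listed people are eligible, so some participants may already be working at T0, and randomisation controls for RTW status. Selection acts mainly on those who return later. The planned model also uses three time points, whereas the calculation uses one. Both points stand and make the figures illustrative.

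3. *The aim is secondary.* Feasibility is the primary outcome, and none of its five criteria uses I-RTW_CS. This stands and limits the severity. A statistical analysis plan, not at hand, might add sensitivity analyses, but the population and the decision rule are already fixed in the protocol.

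4. *A ranked outcome asks a different question.* The sponsor wants more returns and better returns. In simulation (48 versus 24, RTW 70% versus 50%, correlation 0), a ranked outcome is significant in about 30% of trials with no effect on success, and in about 17% when success is truly 0.3 SD worse. The joint rule is met in about 1% or fewer of those trials. With equal RTW and a true +0.5 SD effect on success (correlation 0.5), the ranked outcome detects it in only about 7%. This stands: the ranked outcome cannot simply replace the two components.

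None of the four restores randomisation to a subgroup chosen by a later event, or justifies letting its significance decide effectiveness.

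**Conclusion.** The point holds as a should-fix and a cheap improvement. For participants not working at T0, the second component compares arms in a group formed after randomisation by an outcome that the intervention is hypothesised to change, and the effectiveness rule requires that comparison to be significant.

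Under the stated assumptions the shift runs from +0.09 to -0.21 SD for correlations from -0.3 to 0.7. The RTW rates, correlations and effect size are all assumed.

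Two stronger readings are not supported. A reader might conclude that the rule penalises a toolbox that gets more people back; that depends on a positive correlation that the protocol does not state. A reader might also attribute the low chance of meeting the joint rule to selection; most of it comes from requiring two significant results in a small sample.

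The consequence is confined to the preliminary effect estimate and the sample size for the definitive trial. The feasibility decision is untouched.

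**What to change.** - In Methodology and in the analysis section, state that the returner-only I-RTW_CS comparison is not a randomised comparison, and report it as descriptive.
- In the Project summary and in Study goals and objectives, remove the condition that its significance decides effectiveness. State that it will not alone set the sample size of the definitive trial.
- Add one analysis at T2 in all randomised participants: not returned takes the lowest rank, returners are ordered by I-RTW_CS, and the analysis is stratified by RTW status at T0. Report it with a 95% confidence interval beside both components.

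**Cost.** Wording only; both components are already collected. The downside is real: the ranked outcome is driven largely by RTW, values any return above none, and does not test whether there are both more and better returns. It should accompany the two components and not replace them.

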### Expected outcomes of the study

The study will inform researchers, policy makers and practitioners in the field of occupation health.

### Dissemination of results and publication policy

The results will be disseminated via an article in a peer-reviewed journal related to public health, presentations at several (intern)national conferences and meetings with health care professionals, researchers, employers and policy makers. The scientific journal in which the article will be published will be acknowledged in all these presentations, as well as the sponsor (Dutch Cancer Society), the Dutch online cancer platform ‘kanker.nl’ for its help in recruiting study participants and research assistant [name].

### Duration of the project

Development study protocol & ethics approval: 2018/08/01 - 2019/01/01

Participant recruitment: 2019/0101 - 2019/07/01

Data collection: 2019/01/01 - 2020/01/01

Data analysis: 2020/01/01 – 2020/04/01

Writing manuscript: 2020/04/01 – 2021/01/01

### Ethics

The Executive Board of the Medical Ethics Committee of the Amsterdam UMC, location Academic Medical Center (AMC) will decide whether an extensive test of ethical and juridical aspects is necessary (W18_355 # 18.405, dd. 13/11/2018). We expect that this is not necessary, since the burden for participants will be low and their psychological integrity will not be at stake. Nevertheless, all procedures will be in accordance with the ethical standards of the responsible committees on human experimentation (institutional and national) and with the 1964 Helsinki Declaration and its later amendments, or comparable ethical standards. Before they will be included in the study, informed consent will be obtained from all participants by the executive researcher [name] (see Figure 1 for the procedure).

### Budget

Details available upon reasonable request.

### Other support for the project

N.A.

### Links to other projects

The study is part of the research project ‘The missing link: optimizing return-to-work for employees with cancer, by supporting employers’.

### Curriculum Vitae of investigators

Available upon reasonable request.
